## **PAGE WITH SIGNATURES**

### **TERM OF COMMITMENT, LIABILITY, CONFIDENTIALITY AND RESEARCH GROUP QUALIFICATION**

We, authors of the research “**The Klivo Intervention Program protocol: management of type 2 diabetes mellitus through a digital platform**”, request that the need for signing a written free informed consent be dismissed given that this will be a prospective, observational, and transversal study that will not imply contact between the authors of the research and the participants, and that the authors of the research will not engage in any intervention with the participants. The authors of the research will only analyze the data made available by a partner startup (Klivo), which monitors patients with diabetes mellitus through a digital platform. The protocol developed and operated by the startup Klivo is detailed in the methodology section of this project, but we would like to highlight that the authors of the research will only use the database for statistical analyses, and that the authors will receive de-identified data, while the participants’ identity will remain totally anonymous. In other words, the authors of the research assure the Research Ethics Committee that the participants’ identity will remain anonymous and protected. If any clinical records or other documents are submitted by the partner startup, they will be identified by a code and not by the participant’s name.

We agree to all the provisions listed in the Terms of the Regulating Guidelines and Norms of Research Involving Humans – Resolution 466/12, 251/97, 292/99, 346/05, 340/04, 404/08, 441/11 of the Brazilian National Health Council and National Health Surveillance Agency, and we will make the results of this research public no matter whether they are favorable or not. We will inform this Research Ethics Committee of any alterations, participants’ inclusion or exclusion, amendments, interruptions, and conclusion of the study. We will send reports or copies of scientific communications to the Research Ethics Committee on a regular basis and at the end of the study.

With the signatures of the Authors [name], Main Investigator, <[name]>, and [name], Advisee.

## **ABSTRACT**

Digital therapeutics, an emerging type of medical approach, is defined as evidence-based therapeutic interventions through qualified software programs that help prevent, manage, or treat chronic diseases. These interventions have played an essential role in the management of metabolic conditions, such as type 2 diabetes mellitus, which has high social and economic burden. This study proposes evaluating a digital health strategy in the initial phase of implementation.

### **Methods**

The Klivo Intervention Program is an intensive lifestyle intervention method that seeks to improve the daily lifestyle of adults with type 2 diabetes mellitus, aged  $\geq 18$  years, with glycated hemoglobin (HbA1c) of 7% or higher. The program is free for patients that are users of partner health plans and healthcare provider organizations. HbA1c and time in target blood glucose range will be evaluated at baseline and stipulated time points. The program will be based on a 12-month management process during which participants will be remotely supervised by nurses every fifteen days. When abnormal glucose levels are detected, the participant and their medical doctor will be contacted according to an established protocol. Clinical and laboratory data, weight control, quality of life, mental health, medication adherence, confidence in self-management, healthcare utilization, diabetic literacy and related distress will be evaluated through validated electronic questionnaires. The program will include tele-education via phone calls along the first six weeks. The laboratorial data and data reported over the phone will be assessed at baseline and 3, 6, 9, and 12 months after intervention; the questionnaires will be applied in the first and last months.

### **Expected outcomes**

Findings from this study will provide insights into the health improvement of individuals with type 2 diabetes mellitus and possibly of individuals with other cardiometabolic conditions, including hypertension, dyslipidemia, and obesity.

## **1. INTRODUCTION AND REVIEW OF THE LITERATURE**

Digital therapeutics – an emerging type of medical approach that is expanding globally with market demand – is defined as evidence-based therapeutic interventions through qualified software programs that help prevent, manage, and treat chronic diseases [1]. Some studies have suggested that continuous remote evaluation and daily monitoring can effectively refine the management of chronic conditions such as type 2 diabetes mellitus (T2DM), which has a high prevalence and social and economic burden [2,3]. In this sense, digital therapeutics products addressed to individual needs have contributed to ongoing management of daily life habits and to lowering healthcare costs attributed to chronic metabolic diseases [4,5].

These technologies have improved awareness about diet and regular exercise, optimized glycemic control, and ensured adherence to medication use, consequently lowering the high cost of treating T2DM [6]. Indeed, clinical advancement of participants in protocols such as the Livongo for Diabetes Program has lowered average costs per patient per month by \$83 [7], which is crucial if we consider the estimation that 700 million people will be living with diabetes in 2045 [2]. Therefore, programs that support lifestyle changes can perform secondary prevention by reducing the risk of chronic complications or even primary prevention by delaying disease diagnosis [8].

Some healthcare organizations have offered digital programs as part of the value-based care model [9]. There is a consensus that value is created by enabling health and not by just delivering care. Furthermore, professionals who use digital health technologies benefit from short-term and long-term health improvements [10]. Therefore, here we intend to describe the use of a digital health strategy – the Klivo Intervention Program (KIP) – which is in the initial phase of implementation.

## **2. OBJECTIVES**

### **2.1 Main objective:**

This study will evaluate the self-reported clinical and laboratorial aspects of patients with T2DM recruited for the KIP cohort. Additionally, mental health, medication adherence, confidence in self-management, healthcare utilization, diabetic literacy, and related distress will be evaluated by using validated questionnaires. Two primary outcomes will be evaluated: glycated hemoglobin (HbA1c) and time in range (TIR), defined by the percentage of time an individual remains with blood glucose levels in a target range of 70 to 180 mg/dL.

### **2.2 Specific objectives:**

1. To compare the participant's HbA1c values at baseline and 3, 6, 9, and 12 months after inclusion in KIP.
2. To identify the percentage of time in range (TIR) and, hence, the number of severe hypoglycemic events over 12 months.

### **2.3 Secondary objectives:**

To evaluate the incidence of secondary complications like retinal, renal, cardiac, and cerebrovascular lesions 1 month and 12 months after inclusion in KIP.

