### **Clinical and laboratorial measurements**

#### **Questionnaires**

To obtain information related to the participants' demographic characteristics, medical history, and environmental risk factors, participants will answer questions during a phone call when the nurse will fill in an electronic questionnaire designed according to the ICHOM criteria [12]. Additionally, information about physical activity (time per week), smoking status, and alcohol consumption (amount and frequency per week) will be collected according to the ICHOM criteria [12].

To verify medication adherence, data will be collected via a standardized instrument called the Morisky Green scale [13]. The relationship between participants and T2DM will be evaluated by the Problem Areas in Diabetes (PAID) questionnaire [14]. The WHO Well-Being Index (WHO-5) instrument will be used to assess psychological well-being [15]. The depression status will be estimated by the Patient Health Questionnaire (PHQ-9) [16], and strategic directions will be suggested according to the score.

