#### **Biochemical analysis**

Blood glucose, HbA1c, total cholesterol, triglycerides, and lipoprotein fractions as high-density lipoprotein (HDL-c) and low-density lipoprotein (LDL-c) will be measured by standard techniques in the participants' usual laboratory, after fasting for at least eight hours, every three months.

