#### 4.9 Statistical analysis

**These activities will be performed by the investigator [name]. [name] and her advisee:**

Analyses will be conducted by comparing pre- and post-intervention parameters of the patients selected for KIP.

For all the measurements, clinical and laboratorial characteristics will be assessed by descriptive statistics. Categorical variables will be expressed as percentages, and continuous variables will be expressed as mean  $\pm$  SD or median (interquartile range). The Kolmogorov-Smirnov test will be used to check data normality. The characteristics of the participants in the different groups (defined according to clinical characteristics) will be evaluated by t-test or Wilcoxon rank test (continuous variables) or Pearson's chi-squared test (categorical variables). Logistic regression will be used to assess the association between independent variables and diabetes mellitus. The analyses will be adjusted for age and sex. Receiver Operational Characteristics (ROC) curves will be performed to evaluate the performance of the suggested models and models that are scientifically sound, and the area under the curve (AUC) will be used to measure the discriminatory power of the identified explanatory variables for T2DM. Statistical analysis will be performed by using RStudio software version 1.3.1093. The significance level will be set at 5%.

Sub-groups (e.g., group I and group II) will be created on the basis of pre-existing conditions described as follows:

Group I: Participants with no or only mild non-proliferative diabetic retinopathy without any macular involvement; chronic kidney disease up to stage 3a (eGFR  $\geq 45$  mL/min/1.73 m^2); participants with no known macrovascular diseases.

Group II: Participants with retinal pathologies documented in the medical records, including proliferative diabetic retinopathy (moderate to severe) or other retinal or macular diseases; or chronic kidney disease stage 3b or 4; or known peripheral vascular, coronary, or cerebrovascular disease.

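### The only secondary objective asks for lesion incidence at months 1 and 12, but the planned data can show only newly reported or recorded diagnoses

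*Protocol*

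**What the plan says.** Section 2.3 states one secondary objective: "To evaluate the incidence of secondary complications like retinal, renal, cardiac, and cerebrovascular lesions 1 month and 12 months after inclusion in KIP". Section 3.2 gives no secondary hypothesis, and no expected event rate is stated.

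Section 4.8 sets out what is collected:

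- **Questionnaires.** For demographics, medical history and risk factors, "participants will answer questions during a phone call when the nurse will fill in an electronic questionnaire designed according to the ICHOM criteria". The Methods part of the Abstract adds that "the questionnaires will be applied in the first and last months".
- **Blood pressure and anthropometry.** Both are reported by the participant over the phone.
- **Laboratory.** "Blood glucose, HbA1c, total cholesterol, triglycerides, and lipoprotein fractions as high-density lipoprotein (HDL-c) and low-density lipoprotein (LDL-c) will be measured by standard techniques", every three months.
- **Disease diagnosis.** Definitions are given for hypertension, type 2 diabetes and dyslipidemia only.

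Section 4.9 forms two groups by pre-existing conditions. Group II includes "Participants with retinal pathologies documented in the medical records", chronic kidney disease stage 3b or 4, and known vascular disease. Group I may include mild non-proliferative retinopathy and kidney disease up to stage 3a, and its macrovascular criterion is "participants with no known macrovascular diseases".

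Section 2.1 describes the data openly: "This study will evaluate the self-reported clinical and laboratorial aspects of patients with T2DM recruited for the KIP cohort".

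**The concern.** Incidence of a lesion needs three things: a way of finding the lesion, a definition of a case, and a set of people known to be free of it at the start. The protocol ties none of these to section 2.3. Retinal lesions in particular can be silent, and a person who has had no eye examination cannot report one.

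A published 12-month lesion incidence would then depend on how often participants happened to be examined in usual care and on what they were told and remembered. Because the objective carries the word incidence, a low figure could be read as evidence that few complications arose during the program. The primary outcomes, HbA1c and time in range, are not affected.

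**Working it through.** The protocol gives no incidence, precision or power for this objective, so there is no figure to reproduce. The check sets the objective against each data source and then illustrates the possible bias.

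**Step 1. Which source could supply a case?**

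| Source | Where | Bearing on section 2.3 |
|---|---|---|
| Phone questionnaire with medical history | 4.8 Questionnaires; timing in Abstract, Methods | Can capture a diagnosis the participant knows of, such as a stroke, infarction or diagnosed retinopathy |
| Self-reported blood pressure and anthropometry | 4.8 | None of the lesions |
| Glucose, HbA1c and lipids | 4.8 Biochemical analysis | None of the lesions |
| Medical records | 4.3 (eligibility), 4.9 (groups) | Used at entry; no review at month 12 is described |
| Eye, cardiac or cerebrovascular examination | Not scheduled | None |

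Renal lesions have a similar gap: the laboratory list names no creatinine or albuminuria, although section 4.9 uses eGFR to form the groups.

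**Step 2. Is there a case definition?** No. The Disease diagnosis paragraph covers three conditions, and none is a lesion named in section 2.3.

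**Step 3. Is there an at-risk set?** No. Both groups in section 4.9 can contain participants who already have some retinal or renal disease, and Group II also admits known vascular disease. Section 2.3 excludes none of them.

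**Step 4. What can month 1 mean?** Section 7 collects data at baseline and at 3, 6, 9 and 12 months. The questionnaires fall in the first and last months. The month-1 contact therefore mostly records history at entry, which is existing disease.

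**Step 5. Illustration of size.** Assumptions, none from the documents: true 12-month retinal incidence p = 5%; a fraction e of 30% to 70% examined in usual care; examination finds every lesion; the examined carry the same risk as the rest.

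If the unexamined are counted as negative, apparent incidence = p × e.

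- e = 30%: 5% × 0.30 = 1.5%
- e = 50%: 5% × 0.50 = 2.5%
- e = 70%: 5% × 0.70 = 3.5%

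The relative shortfall is 1 − e, that is 70%, 50% and 30%, whatever the value of p.

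If only the examined are counted, with 100 participants (the recruitment minimum in section 4.2, taken here as all free of retinal disease at entry), the expected result is 1.5/30 = 5% at e = 30% and 3.5/70 = 5% at e = 70%. The shortfall goes, but the denominator falls to 30 or 70.

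**Step 6. Precision even with complete examination.** With 0 cases in 100, the exact two-sided 95% upper limit is 1 − 0.025^(1/100) = 3.6%. With 5 in 100, the exact interval is 1.6% to 11.3%.

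**The case against.** The strongest reply is that section 2.3 already means reported history. The questionnaires fall in the first and last months, matching months 1 and 12; they record medical history; and section 2.1 calls the clinical data self-reported. On that reading one source serves both ends and can capture diagnosed events. This stands in part. It shows that a reader who infers that nothing scheduled could ever pick up a complication goes too far. It does not turn reported diagnoses into lesion incidence, and the protocol never links the questionnaire to this objective.

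Two other stronger readings are tempting, and the documents do not support them.

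- A reader might infer that unexamined participants will be scored as lesion-free. No coding rule is stated. Setting them to missing is equally compatible with the text, and a statistical analysis plan that is not at hand may settle it. What can be said is that they are at risk of being counted that way, because nothing separates not examined from no lesion.
- A reader might infer that known disease will appear as new because entry status comes from records and month-12 status from the phone. Section 4.9 uses records to define a subgroup, not the baseline for section 2.3, so no such switch is specified.

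Records are also not ruled out as a follow-up source: the opening Term of Commitment allows that the startup might submit clinical records. That is a conditional remark and not a scheduled review.

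Finally, the study is observational, with no secondary hypothesis, so the matter could be called wording. That bears on severity. An analysis plan can settle coding, but it cannot supply examinations that were never scheduled.

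**Conclusion.** The point holds as a mismatch between objective and data. As written, section 2.3 promises lesion incidence, and the plan can deliver newly reported or recorded diagnoses only. This applies to every participant, since no relevant examination is scheduled for anyone; it does not mean that every participant would be misclassified.

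The likely error for silent lesions is undercounting, but its size cannot be fixed from the documents. The range of 1.5% to 3.5% against an assumed 5% is an illustration. It rests on the assumed examination rate and on the unexamined being counted as negative. The concern is strongest for retinal lesions and weaker for cardiac and cerebrovascular events that present clinically.

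The protocol should be changed here because the change alters what the secondary result may claim. The primary outcomes stand apart from it.

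**What to change.** Restate section 2.3 as complications newly diagnosed between inclusion and month 12, as reported in the first- and last-month questionnaires. If the partner insurers confirm that a month-12 extract is available, medical records may be named as the source instead. In either case:

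1. Use the same source at both time points.
2. Treat the first-month contact as entry status, and say so, so that month 1 is no longer presented as a separate incidence figure.
3. For each complication, restrict the denominator to participants without it at entry.
4. For every complication type, keep participants with no assessment in the period as 'not assessed', and report the number assessed beside the result.
5. State that the result is not to be interpreted as lesion incidence.

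Cost: mainly a wording change, with no new examination. Item 4 needs the chosen source to show whether an assessment took place; the protocol does not say whether the questionnaire asks this, so a question may have to be added. The month-12 extract must be confirmed before it is relied on, since the documents show records used only for eligibility and grouping. The downside is a smaller, selected denominator and a more modest secondary conclusion, and both should be stated with the result.

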### **3. RESEARCH HYPOTHESES**

#### **3.1 Main hypothesis:**

KIP participants should present improved HbA1c and TIR along the intervention as compared to baseline values.

#### **3.2 Secondary hypothesis:**

None

#### **3.3 Research variables:**

- dependent variable(s) (outcomes): HbA1c and time in range (TIR, percentage of time an individual remains with blood glucose levels in a target range of 70 to 180 mg/dL)
- independent variables (causes): non-applicable
- interfering variables (causes): non-applicable
- control variables (causes): non-applicable

## 4. STUDY OF CASES AND METHOD

### 4.1 Study type and design:

Prospective, observational, and transversal study.

### 4.2 Population and sampling:

All the patients enrolled for KIP will be considered for the cohort, except patients who refuse to share their data or lose follow-up. Patients of both sexes and aged  $\geq 18$  years will be included. We aim to recruit at least 100 participants.

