### 4.3 Inclusion and exclusion criteria:

#### **Inclusion criteria**

1. Diagnosis of T2DM in the electronic medical record of private health insurance companies (HbA1c reading 7% or higher; age  $\geq 18$  years).
2. Willingness to receive phone calls and messages for monitoring the disease and for tele-education.
3. Willingness to use the standard monitoring devices (glucometer), synchronized with the telemonitoring system according to the study protocol throughout the 12-month study period.

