## 7. TIME SCHEDULE

|                                                   | 2022           |   |   |   |   |   |   |   |   |   | 2023 |   |
|---------------------------------------------------|----------------|---|---|---|---|---|---|---|---|---|------|---|
|                                                   | M              | A | M | J | J | A | S | O | N | D | J    | F |
| Specification of objectives and hypotheses.       |                |   |   |   |   |   |   |   |   |   |      |   |
| Survey of the literature.                         |                |   |   |   |   |   |   |   |   |   |      |   |
| Project approval by funding agencies              |                |   |   |   |   |   |   |   |   |   |      |   |
| Project approval by the Research Ethics Committee |                |   |   |   |   |   |   |   |   |   |      |   |
| Operating concepts and variables.                 |                |   |   |   |   |   |   |   |   |   |      |   |
| Data collection.                                  |                |   |   |   |   |   |   |   |   |   |      |   |
| Laboratory tests (if applicable)                  | NON-APPLICABLE |   |   |   |   |   |   |   |   |   |      |   |
| Data compilation.                                 |                |   |   |   |   |   |   |   |   |   |      |   |
| Results analysis.                                 |                |   |   |   |   |   |   |   |   |   |      |   |
| Statistical treatment and data analysis           |                |   |   |   |   |   |   |   |   |   |      |   |
| Discussion and conclusion                         |                |   |   |   |   |   |   |   |   |   |      |   |
| Thesis defense/Presentation                       |                |   |   |   |   |   |   |   |   |   |      |   |
| Publication in scientific journals.               |                |   |   |   |   |   |   |   |   |   |      |   |

Data collection at baseline and the intervention will start on 03/03/2022. Data will be collected again 3, 6, 9, and 12 months after the start of the protocol.

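### The cohort definition leaves out enrolled participants who are lost to follow-up, so the HbA1c and TIR changes would describe only those retained and are likely, though not certain, to overstate improvement

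*Protocol*

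**What the plan says.** Section 4.2 of the protocol (Population and sampling) considers all patients enrolled in the Klivo Intervention Program (KIP) for the cohort, "except patients who refuse to share their data or lose follow-up". It then gives the recruitment target: "We aim to recruit at least 100 participants". It does not say what counts as lost: no visit, window or number of missed contacts is given. Nor does it say whether the target is before or after loss.

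The main hypothesis (section 3.1) is about a wider group: "KIP participants should present improved HbA1c and TIR along the intervention as compared to baseline values". Section 4.9 also refers to a wider group: "Analyses will be conducted by comparing pre- and post-intervention parameters of the patients selected for KIP". Section 7 sets the repeat visits: "Data will be collected again 3, 6, 9, and 12 months after the start of the protocol". HbA1c and TIR are the two primary outcomes (section 2.1). There is no control group.

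Nowhere does the protocol offset the exclusion. It has no all-enrolled analysis, no comparison of lost with retained participants, and no expected dropout rate.

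**The concern.** Refusing to share data is settled at entry and is a consent matter. Loss to follow-up is different: it can be known only after enrolment and may depend on how the participant is doing. Writing it into the cohort definition makes the analysis set conditional on staying in the programme.

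Two features make this matter here. First, the design is a single-cohort comparison with baseline, so there is no comparator arm in which similar attrition might partly cancel. Second, staying takes engagement: nurse calls every two weeks for a year, and a synchronised glucometer that the participant must keep using. Those who leave receive less of the programme and plausibly improve less.

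The choice also cannot be left to a statistical analysis plan. Such a plan may decide how to handle missing values, but only for people who are in the population. Section 4.2 removes these participants first. The same exclusion would carry over to the severe hypoglycaemia counts (section 2.2) and the 12-month complications (section 2.3).

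**Working it through.** **Plan's own figure.** The only figure is the target of at least 100 recruited. No effect size, SD, power or dropout rate is given, so there is nothing to reproduce. The dropout rates, mean changes, SDs and odds ratios below are assumptions.

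**Formula.** Let p be the proportion lost, R the mean improvement (fall in HbA1c) in those retained, and L the mean improvement in those lost.

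- Mean in all enrolled = (1 − p) × R + p × L
- Bias of the retained-only mean = R − [(1 − p) × R + p × L] = p × (R − L)

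The number recruited does not enter, so a larger cohort does not reduce the bias.

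**Size if those lost improve less.** Assume p = 20-40% and R − L = 0.3-0.8 HbA1c points.

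| Loss | R − L = 0.3 | R − L = 0.8 |
|---|---|---|
| 20% | 0.20 × 0.3 = 0.06 | 0.20 × 0.8 = 0.16 |
| 40% | 0.40 × 0.3 = 0.12 | 0.40 × 0.8 = 0.32 |

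**Random error at the matching sample size.** With 100 recruited, 20% loss leaves 80 and 40% leaves 60. The 95% half-width is t × SD/√n, with an assumed SD of change of 1.2-1.5.

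- n = 80: 1.990 × 1.2/√80 = 0.27; 1.990 × 1.5/√80 = 0.33
- n = 60: 2.001 × 1.2/√60 = 0.31; 2.001 × 1.5/√60 = 0.39

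The bias therefore runs from about a fifth of the half-width (0.06 against 0.27-0.33) to about the same size (0.32 against 0.31-0.39).

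**Other directions.** The table enters only positive differences. To show the other signs, assume that those retained improve by 1.0 point and that 40% are lost.

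| Change in those lost | Bias of the retained-only mean |
|---|---|
| Worsen by 0.3 | 0.40 × 1.3 = 0.52 overstated |
| No change | 0.40 × 1.0 = 0.40 overstated |
| Improve by 1.0 | 0 |
| Improve by 1.3 | 0.40 × 0.3 = 0.12 understated |

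For TIR, if those retained gain 10 percentage points and those lost gain none, 20-40% loss overstates the gain by 2-4 percentage points.

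**Selection alone, with no true change.** In a simulation, change has mean 0 and SD 1.3, 100 are recruited, and the odds of staying depend on the change. The last column is the rejection rate of a two-sided 5% test, by normal approximation.

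| Odds ratio of staying per 1-point fall | Loss | Mean change in those retained | Rejection |
|---|---|---|---|
| 1.0 | 20% or 30% | 0.00 | 5% |
| 1.5 | 20% | −0.13 | 15% |
| 1.5 | 30% | −0.19 | 25% |
| 0.8 | 20% | +0.08 | 8% |
| 0.8 | 30% | +0.11 | 11% |

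If staying is even moderately related to response, the retained group can show a change that the programme did not produce. If the relation runs the other way, it shows an apparent worsening.

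**The case against.** The strongest objections concern how far the text can be pushed, and several stand.

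- **Direction.** A reader might infer that the analysis will overstate improvement. The protocol gives no dropout rate, no reasons for loss and no outcomes in those lost. Overstatement is a reasonable inference from the demands of the programme, but the documents do not establish it.
- **Interim values.** A reader might infer that 3-, 6- and 9-month values of lost participants would be thrown away. That follows only if being lost means missing the 12-month value. The term is undefined and the document is a translation. It could instead mean having no post-baseline data, in which case participants with interim values stay in and the bias is probably smaller. Specific objective 1 in section 2.2 does use the interim visits.
- **Section 4.9.** A reader might take its pre-post comparison as confirming a completers-only analysis. It does not: it speaks of the patients selected for the programme, which reads at least as easily as everyone selected. It disagrees with section 4.2 rather than supporting it.
- **Intensity of device use.** The protocol requires a synchronised glucometer throughout the study period but sets no measurement frequency. The argument may rest on sustained use, not on daily use.
- **Role of the analysis plan.** The model, the sensitivity analyses and the reporting by visit could properly be left to a statistical analysis plan, which is not at hand.

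None of this removes the core point. On either reading of the undefined term, section 4.2 excludes enrolled participants because of a later event, and no later analysis method can use people who are outside the population.

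**Conclusion.** The point holds as a fault in the population definition. Section 4.2 conditions the cohort on retention, leaves retention undefined, and does not match the groups named in sections 3.1 and 4.9. It should be corrected before analysis because it decides who enters both primary analyses.

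Confidence is high that the exclusion exists, and lower on its effect. Overstated improvement is likely but not demonstrable from the protocol. The range of 0.06-0.32 HbA1c points in favour of the programme rests on assumed loss of 20-40% and an assumed 0.3-0.8 point smaller improvement in those lost. The comparison half-width of about 0.27-0.39 rests on an assumed SD of change of 1.2-1.5 and 60-80 retained of 100.

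**What to change.** 1. Rewrite section 4.2 so that the analysis cohort is every enrolled participant who authorises data use and has a baseline value of the outcome analysed (HbA1c or TIR), regardless of later follow-up.
2. Define loss to follow-up, naming the visit and window that decide it, and state whether the target of 100 is before or after loss.
3. Reconcile sections 4.2 and 4.9 so that both name the same group as the hypothesis in section 3.1.
4. In the protocol or the analysis plan, analyse all available 3-, 6-, 9- and 12-month values, for example with a likelihood-based mixed model. Such a model relies on loss being explained by the observed data, so add a sensitivity analysis that covers both no change and worsening in those lost. A no-change assumption alone does not bound the bias.
5. Report the numbers lost by visit, with their baseline values.

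The cost is a change of wording and slightly more analysis, with no new data collection. The reported improvement will probably be somewhat smaller.
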